## ENDOVASCULAR TREATMENT

Endovascular treatment is an established treatment strategy for patients with symptomatic PAD and aortoiliac occlusive disease in the NHS. The exact type of procedure offered to each patient will be decided locally, based on clinicians’ preferences and patient characteristics. Any type of angioplasty device, stent, vessel preparation strategy, or other adjunct endovascular procedure can be used, at the discretion of the clinicians at each trial site. Inflow and outflow procedures, including open surgical access to arteries or open surgical reconstruction to ensure adequate inflow/outflow will be allowed.

For both open surgery and endovascular treatment, inflow and outflow procedures (e.g. adjunct open surgery when undergoing endovascular treatment or vice versa) will be left to the treating clinicians to decide/offer.

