## Withdrawal of participation and consent criteria

Participants may withdraw their consent for the trial at any time if they choose not to continue, without prejudice for future care and they do not need to provide a reason why. However, if they are willing to provide a reason, it should be recorded on the relevant CRF. Participants will be asked to what extent they wish to withdraw their consent from the trial:

Prior to trial intervention, i.e., withdrawal from the trial intervention:

The participant would like to withdraw from their randomly allocated trial treatment i.e., they will not undergo the type of surgery as determined by randomisation, but will remain in trial follow-up and data will continue to be collected from them.

Post-trial intervention:

- Participant would like to withdraw from the attendance at clinic visits but gives permission for the trial related data to be collected from medical notes, NHS digital or contacted remotely (e.g., via telephone) to collect trial data
- Participant would like to withdraw from all trial assessments (both in person and remotely) but is happy for the study team to collect data from NHS databases in the future
- Participant would like to withdraw from the trial completely – no further data collection will be carried out

Withdrawal status will be documented on trial CRF and medical records. It is important to note that the data already collected prior to the point of withdrawal can still be analysed and included in the trial dataset.

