### Reporting Procedures for Serious Adverse Events

Adverse events which meet the serious criteria (SAEs) and which are deemed related to the trial, except those identified as expected within section 9.1, occurring from point of randomisation and until follow-up completion (minimum of two years after trial treatment), must be reported to the Sponsor and the EVOCC trial management team immediately and within 24 hours of becoming aware of the event. The SAE will be reported using the current standard Sponsor SAE reporting form and according to the Sponsor SOP for reporting serious adverse events. For clarity, those listed in the above table as expected SAEs and SAEs that are deemed as **not** related to the trial do not need to be reported, only those events that fall outside of this list should be reported expediently as described. All exempt SAEs should be recorded in the patient medical notes as such.

**Please note:** **No serious adverse reactions (SARs) are anticipated as a unique consequence of participation in the EVOCC trial.**

The following information will be recorded for all SAEs:

- Description of the event
- Date of onset and end date
- Severity
- Assessment of relatedness to trial
- Action taken.

SAEs will be followed until resolution or the event is considered stable.

It will be left to the investigator’s clinical judgment whether or not an SAE is of sufficient severity to require the participant’s removal from the trial. The participant must undergo an end of trial assessment and be given appropriate care under medical supervision until symptoms cease or the condition becomes stable. The severity of events will be assessed on the following scale: 1 = mild, 2 = moderate, 3 = severe. The relationship of SAEs to the trial will be assessed by a medically qualified investigator.

Additional information will be provided if requested to the Sponsor and main Research Ethics Committee (REC). The Principal Investigator or another delegated physician (as agreed by the Sponsor) is responsible for the review and sign off of the SAE and the assessment of causality.

The Sponsor will perform an initial check of the information and ensure that the SAE line listing is reviewed by the Director of Research & Innovation. All SAE information must be recorded on an SAE form and sent to the Sponsor. Additional information received for a case (follow-up or corrections to the original case) needs to be detailed on a new SAE form and sent to the Sponsor.

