### ADVERSE EVENTS REPORTING

Unexpected serious adverse events (SAEs) outside of the list provided in section 9.1, will be reported descriptively in the safety population i.e., participants undergoing trial treatment, presented in groups according to treatment received not as randomised. The number of unexpected serious adverse events and the number of participants experiencing unexpected serious adverse events will be presented categorised by common SAE terms. Unexpected serious adverse events will be presented as line listings and grouped by severity.

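### The only stated table of unexpected SAEs omits never-treated participants and groups the rest by treatment received; an as-randomised table should stand beside it

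*Protocol*

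**What the plan says.** Four parts of the protocol bear on this.

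- **Who is tabulated, and in which column.** Section 11.6.3 says: "Unexpected serious adverse events (SAEs) outside of the list provided in section 9.1, will be reported descriptively". The table is built "in the safety population i.e., participants undergoing trial treatment, presented in groups according to treatment received not as randomised". No second table by allocated arm is stated.
- **When collection starts.** Section 9.2.2 covers events "occurring from point of randomisation and until follow-up completion".
- **Which events are collected.** The same section limits reporting to "Adverse events which meet the serious criteria (SAEs) and which are deemed related to the trial, except those identified as expected within section 9.1".
- **Deviation from allocation is foreseen.** Section 8.7 describes participants who withdraw from their allocated treatment: "they will not undergo the type of surgery as determined by randomisation, but will remain in trial follow-up". The screening log in section 5.1.1 also counts how many accept their allocation. Neither section gives an expected number.

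Section 11.5 analyses the primary outcome (death or major amputation) by intention to treat. Section 11.6 places the secondary outcomes in the intention-to-treat population, although it also calls them complete-case. Under section 4.2 these include all-cause mortality, cardiovascular events, admissions, re-interventions and all lower limb amputations.

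**The concern.** Collection and tabulation do not match. A reportable SAE between randomisation and treatment is collected, but if the participant is never treated it has no place in the table. A participant who switches is counted under the other treatment. The trial is open label and allocation is known before treatment, so both kinds of deviation can depend on the arm and on the patient's prognosis. The two columns are then no longer the randomised groups, and a difference between them can arise from selection alone.

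What is at stake is limited but real. The table of unexpected SAEs will be read next to outcomes analysed as randomised. As section 11.6.3 is worded, a reader has no as-randomised version to check it against.

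**Working it through.** **Inputs from the protocol.** Section 11.1 gives 596 participants before 5% loss: 596 / 0.95 = 627.4, rounded up to 628, or 314 per arm. This reproduces the stated sample size. Allocation is 1:1.

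**Inputs that are assumed.** The protocol gives no rate for never being treated, for switching or for reportable SAEs. I assume an SAE risk p = 5% in ordinary patients and r × p in those who deviate, with r = 1, 2 or 3. Each patient's risk is the same whichever arm they are in, so the true ratio is 1.00.

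**Formulas.** Let a be the fraction who, if allocated open surgery, are never treated, and c the fraction who, if allocated open surgery, switch to endovascular treatment.

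- True risk in each randomised arm: R = (a + c)·r·p + (1 − a − c)·p
- Open column as tabulated: risk p, in 314(1 − a − c) people
- Endovascular column as tabulated: risk (R + c·r·p) / (1 + c), in 314(1 + c) people

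For a switch from endovascular to open, exchange the columns.

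**Worked example** (a = 5%, c = 10%, r = 3). R = 0.15 × 0.15 + 0.85 × 0.05 = 6.5%, or 20.4 patients per randomised arm. The open column shows 5.0% of 267 (13.3 patients). The endovascular column shows (0.065 + 0.015) / 1.10 = 7.3% of 345 (25.1 patients). About 16 participants, carrying 2.4 patients with an SAE, are in neither column. The ratio is 0.050 / 0.0727 = 0.69.

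| Assumed deviation | r | True risk, both arms | Shown: open | Shown: endovascular | Ratio |
|---|---|---|---|---|---|
| 2% of open arm never treated | 2 | 5.1% | 5.0% | 5.1% | 0.98 |
| 5% of open arm never treated | 3 | 5.5% | 5.0% | 5.5% | 0.91 |
| 5% switch open to endovascular | 2 | 5.25% | 5.0% | 5.5% | 0.91 |
| 10% switch open to endovascular | 3 | 6.0% | 5.0% | 6.8% | 0.73 |
| 5% never treated and 10% switch from open | 3 | 6.5% | 5.0% | 7.3% | 0.69 |
| 5% switch endovascular to open | 2 | 5.25% | 5.5% | 5.0% | 1.10 |
| 10% switch endovascular to open | 3 | 6.0% | 6.8% | 5.0% | 1.36 |
| 5% never treated and 10% switch from open | 1 | 5.0% | 5.0% | 5.0% | 1.00 |

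Tabulated by randomised group in all 628, the ratio is 1.00 in every row. Most of the shift comes from switching: adding 5% never treated to 10% switching moves the ratio only from 0.73 to 0.69.

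**A second set of assumptions.** Take 30% of patients as frail, with SAE risks of 15% (frail) and 5% (others). Let 80% of those switching from open be frail, and let 3% switch the other way at average frailty. At 10% switching from open:

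- Open column: 71.9 frail and 220.1 others, so 21.8 / 292.0 = 7.5%
- Endovascular column: 116.5 frail and 219.5 others, so 28.4 / 336.0 = 8.5%

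The ratio is 0.88, against 25.1 patients with an SAE in each randomised arm. The shift is about 3 patients per column.

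**The case against.** The case on the other side is strong on several points.

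- **Scope.** A reader might infer that the trial's safety comparison as a whole is non-randomised, so that benefit and harm cannot be weighed together. The protocol does not support that. The main harms are primary or secondary outcomes analysed by allocation, and section 11.6.3 governs only a residual descriptive table without a test. A death while waiting for treatment is a primary outcome event and is not lost.
- **Never-treated participants.** Only SAEs judged related to the trial and absent from the long expected list are reportable. Deterioration before any procedure would seldom qualify, so the never-treated rows above probably overstate that effect. The annual ethics report and the data monitoring committee's cumulative review (section 9.2.2) are not restricted to treated participants.
- **Direction.** A reader might infer that the rule flatters open surgery. That requires frailer patients to leave open surgery. Entry requires suitability for either treatment and a multidisciplinary team in equipoise, and the focus groups preferred endovascular treatment, so refusing open surgery may reflect preference rather than frailty. The opposite switch makes open surgery look worse.
- **Meaning of treatment received.** Section 7.2 leaves adjuncts to the treating clinicians ("e.g. adjunct open surgery when undergoing endovascular treatment or vice versa"), and section 11.1 expects 43% of endovascular patients to need re-intervention within 3 years. A reader might infer that patients change columns for these reasons. But Table 2 has a single trial-intervention time point, so the index procedure is the natural reading. Adjuncts are permitted within each strategy, and re-interventions are on the expected list and counted as a secondary outcome.
- **Convention.** An as-treated safety table is common and attributes procedural complications to the procedure performed. The statistical analysis plan is not shown and may add an as-randomised table.

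All of this narrows the point. What remains is that the one stated comparison of unexpected SAEs omits randomised participants whose reportable events are collected, and that its wording sets aside grouping by allocation.

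**Conclusion.** The point holds in a narrow form. Section 11.6.3 fixes a descriptive table of unexpected SAEs on a population and grouping determined after randomisation, while sections 9.2.2 and 8.7 provide for collection from randomisation and for continued follow-up of those who do not take their allocation. With equal true risk, the open/endovascular ratio can appear anywhere from about 0.69 to 1.36, depending on who deviates and in which direction, and it stays at 1.00 if deviation is unrelated to risk. These figures rest on assumed rates of deviation and SAEs. In the 10% case of the second set of assumptions the shift is about 3 patients per column. Neither the size nor the direction can be predicted from the protocol, and the outcomes analysed by intention to treat are untouched. This is a cheap improvement to the safety reporting and does not threaten the trial's main conclusions.

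**What to change.** Keep the as-treated table, since it serves attribution, and state that it groups treated participants by the index procedure performed. Then add to section 11.6.3:

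> Unexpected SAEs will also be presented for all randomised participants by randomised group, counted from randomisation.

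The cost is one sentence of wording and one extra descriptive table from data already held. The downside is that in the added table a few SAEs will follow a procedure other than the one allocated; the as-treated table shows those under the procedure performed. If the statistical analysis plan already contains such a table, only the protocol wording needs aligning with it.

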### Procedure(s) to account for missing or spurious data

Missing data is expected to be minimal given the type and mode of data collected. The primary outcome other time-to-event outcomes will not encounter missing data due the nature of the data. Furthermore, any losses to follow-up should be minimised by the intended methods to capture long term follow-up through routine data capture.

### Economic evaluation

A prospectively planned economic evaluation will be conducted from an NHS and personal social services perspective, as per National Institute of Care Excellence (NICE) recommendations (21), led by Health Economists with considerable experience in NIHR HTA funded vascular research. Use of hospital and community services will be recorded over the trial time horizon using the trial CRFs. Quality-of-life will be assessed using the EQ-5D-5L, converted to health utility scores using the UK value set recommended by NICE. Unit costs will be based on manufacturers’ prices and national databases. Days lost from work and activities will be recorded and used in a secondary analysis. The extent and pattern of missing data will be assessed and appropriate methods employed, for example, multiple imputation.

If the trial finds a clinically meaningful difference in outcomes or costs over the study time horizon, a decision model will be constructed to take account of the loss in life years and long-term impact on quality-of-life after complications. A state-transition decision model (Markov model) will estimate costs and QALYs over the lifetime of the cohort. The recommended discount rate of 3.5% per year will be used. Parametric survival curves will be used to estimate rates of death, cardiovascular disease and amputation events. Long term rates of events will be estimated based on extrapolation of study data and literature. Outcomes or states of the model will be decided based on consultation with experts and review of previous economic evaluations in PAD. Tunnel states may be used if time to death following non-fatal events is time-varying. Sensitivity analyses will be conducted by varying key variables with high uncertainty. The model will be constructed, analysed, and reported, according to CHEERS guidelines (22).

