**TRIAL SUMMARY**

| **Trial Title** | A randomised controlled trial assessing the clinical and cost-effectiveness of Endovascular vs. Open revascularisation in severe oCClusive aorto-iliac disease. (**EVOCC)** | |
| --- | --- | --- |
| **Trial Design** | A parallel group, multicentre, prospective, open label, randomised controlled trial (with an internal pilot) of endovascular vs. open revascularisation in patients with severe oCClusive aorto-iliac disease. | |
| **Participating Sites:** | Over 30 NHS hospital sites in the UK (England, Scotland and Wales) | |
| **Trial Participants** | Adult patients with symptomatic peripheral arterial disease who have severe aorto-iliac occlusive disease (TASC II class C or D) and are undergoing revascularisation of their aorta/iliac arteries | |
| **Planned Sample Size** | 628 | |
| **Recruitment Period** | 6 month pilot recruitment phase and 24 months for the main recruitment phase. | |
| **Follow Up Duration** | Minimum 2 years (maximum 4.5 years, median 3 years) | |
| **Planned Trial Period** | **Grant start date**: 01/01/2023  Total grant duration 69 months, including 6 month pilot recruitment, 24 months main recruitment and 24 months of patient follow-up. | |
|  | **Objectives** | **Outcome Measures** |
| **Primary** | Establish whether the clinical and cost-effectiveness of open surgery for severe occlusive aorto-iliac disease (TASC II C/D) is superior to endovascular treatment? | Combined measure of death or major lower limb amputation, measured in days from randomisation until first event or until the end of the trial (minimum 2 years) where no event occurs |

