## Economic impact and cost effectiveness

We obtained information from our published meta-analysis (1) and HES to identify patients with CLTI/claudication and TASC C/D aorto-iliac disease who had revascularisation between 2014-2019. We then constructed an early decision model to calculate 3 year death, amputation, and re-intervention rates, NHS resource use, and quality-adjusted life years (QALYs). Open surgery is associated with a peri-operative mortality of 3% vs. 1% for endovascular treatment. The latter is associated with more re-interventions and late amputations/deaths. Three year survival is 70% for open surgery vs. 65% for endovascular treatment (HES data). Open surgery costs arise from intensive care stay and early complications. Endovascular treatment costs arise from devices, re-interventions, and late amputations. Average peri-operative and device costs are £13,765 for endovascular treatment. Late re-interventions and amputations cost £6,811, totalling £20,576 for endovascular treatment over 3 years. Open surgery costs £10,675 over 3 years (£9,901 less per patient). The 3 year QALY difference is 0.153, favouring open surgery, despite the higher immediate mortality/morbidity. All of these estimates, however, are based on unadjusted observational data. Overall, it is very uncertain whether endovascular treatment, despite being minimally invasive, is cost-effective in the NHS.

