## Primary objective

To identify whether the clinical and cost-effectiveness of open surgery for severe occlusive disease (TASC II C/D) of the aorta and iliac arteries is superior to endovascular treatment.

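### The lifetime cost-effectiveness model is built only if the trial shows a meaningful difference in outcomes or costs, so the horizon of the economic answer depends on the observed result

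*Protocol*

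**What the plan says.** Section 3.2 puts cost-effectiveness in the primary objective, which opens: "To identify whether the clinical and cost-effectiveness of open surgery for severe occlusive disease". The comparison it goes on to set is one of superiority over the endovascular arm. The research question in section 3.1 is framed the same way.

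Section 11.6.5 then plans the economic evaluation in two stages.

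- **Within-trial stage, unconditional.** "Use of hospital and community services will be recorded over the trial time horizon using the trial CRFs". The Trial Summary gives follow-up as at least 2 years and at most 4.5, with a median of 3.
- **Lifetime stage, conditional.** "If the trial finds a clinically meaningful difference in outcomes or costs over the study time horizon, a decision model will be constructed". Its stated purpose is to account for lost life years and for the lasting effect of complications on quality of life. If built, "A state-transition decision model (Markov model) will estimate costs and QALYs over the lifetime of the cohort", discounted at 3.5% per year.

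No other part of the protocol commits to a horizon beyond the trial, and section 11.6.5 does not say what follows if the condition fails.

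On the expected timing of events, section 2.2 says: "Open surgery is associated with a peri-operative mortality of 3% vs. 1% for endovascular treatment". It adds that endovascular treatment brings more re-interventions and more late amputations and deaths, and that "Three year survival is 70% for open surgery vs. 65% for endovascular treatment (HES data"). It also gives a 3-year QALY difference of 0.153 in favour of surgery, and describes all these estimates as unadjusted and observational.

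**The concern.** A cost-effectiveness decision rests on expected costs and QALYs and their uncertainty, over a horizon long enough to hold the important differences. Failing to see a meaningful difference within the trial does not make expected lifetime costs and QALYs equal. Under the present rule the horizon is chosen after the result is known, for a question that belongs to the primary objective.

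The timing of events makes this more than a matter of form. The protocol expects one arm to lose patients early and the other to lose patients and limbs late. With that pattern, totals at a median of 3 years can look alike while the survivors in the two arms have different prospects. That is the situation in which neither limb of the condition might be met, and in which a longer horizon would be most informative. A threshold set in an analysis plan would make the rule clearer, but the horizon would still depend on the result.

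**Working it through.** **1. The protocol's own cost figures (section 2.2).**
- Endovascular: £13,765 (peri-operative and device) + £6,811 (late re-interventions and amputations) = £20,576 over 3 years, as stated.
- Difference from open surgery: £20,576 − £10,675 = £9,901, as stated.

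The condition is met by a difference in outcomes or in costs. If a cost difference of this order appears in the trial, the cost limb alone would very probably lead to the model being built.

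**2. How firmly the outcome limb can be expected to be met.** No threshold is given, so no probability can be calculated. The sampling error of the observed result can be. Take 3-year survival of 70% and 65% (section 2.2) and 314 per arm (section 11.1), as simple proportions without censoring:

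SE = √(0.70×0.30/314 + 0.65×0.35/314) = √(0.4375/314) = 0.037, or 3.7 points.

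The observed gap therefore carries a 95% margin of about ±1.96 × 3.7 = ±7.3 points around a true gap of 5. The outcome limb depends on a noisy quantity and could go either way.

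**3. What could lie beyond the trial horizon.** The inputs are a survival gap g at 3 years, L further years lived by each extra survivor, a utility of 0.6, and discounting at 3.5% back to randomisation. The discount rate is from section 11.6.5. L and the utility are assumptions that the protocol does not supply.

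QALYs per patient after year 3 = g × 0.6 × A(L), where A(L) = (1.035^−3 − 1.035^−(3+L)) / ln 1.035 and ln 1.035 = 0.0344.

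| Further years L | A(L) | g = 5 points | g = 1 point |
| --- | --- | --- | --- |
| 3 | (0.9019 − 0.8135)/0.0344 = 2.57 | 0.077 | 0.015 |
| 5 | (0.9019 − 0.7594)/0.0344 = 4.14 | 0.124 | 0.025 |
| 8 | (0.9019 − 0.6849)/0.0344 = 6.31 | 0.189 | 0.038 |

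The 5-point column uses the HES gap in section 2.2. The 1-point column is chosen to represent a trial with little difference in survival. For comparison, the protocol expects a QALY difference of 0.153 over the first 3 years.

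The 5-point column belongs to the scenario that also carries the £9,901 cost difference, in which the model would probably be built and nothing lost. The 1-point column is nearer to a trial in which the condition fails. It counts only the further life of extra survivors, and leaves out later differences in amputation, re-intervention, mortality rates and costs.

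**The case against.** The strongest reply is that the condition has two limbs and the second will probably be met. With £9,901 expected between the arms, the lifetime model is likely to be built. This stands, and it keeps the point small. It does not remove the dependence on the result, because the cost estimate comes from data that the protocol itself calls unadjusted and observational.

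A second reply is that the within-trial evaluation is unconditional and the condition is stated in advance, so nothing is hidden. This also stands: a reader might infer selective reporting, and the text does not support that. Nor is the missing numerical threshold a fault in itself, since a statistical or health economics plan could supply it. The difficulty is the conditional rule, which the protocol fixes.

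Two stronger readings should be set aside.

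- **That stopping at the trial horizon biases the answer against surgery.** Early deaths do count against surgery (3% vs 1%). Early costs do not: endovascular peri-operative and device costs (£13,765) exceed the whole 3-year cost of surgery (£10,675). On section 2.2's figures surgery is already cheaper and better at 3 years, so a short horizon would not reverse that answer. What is lost could favour either arm.
- **That the model must first pass a significance test on clinical outcomes.** The text speaks of a clinically meaningful difference, not a statistically significant one, and includes costs.

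**Conclusion.** The point holds in a limited form. The protocol makes the horizon of its cost-effectiveness answer depend on the observed result, and no fallback beyond follow-up is stated. On the protocol's own expectations the model would probably be built, so this is a low-severity point. It affects no sample size, type I error rate or clinical analysis.

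The amount at stake when the model is skipped cannot be fixed from the documents. Under the stated assumptions (utility 0.6, 3 to 8 further years, 3.5% discounting), survival gaps of 1 to 5 points at 3 years correspond to roughly 0.015 to 0.19 QALY per patient after year 3. The lower end is nearer to the case in which the condition would fail. These figures show scale and are not estimates of bias.

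**What to change.** In section 11.6.5, delete the conditional clause and state the commitment outright, for example: *A state-transition model will estimate lifetime costs and QALYs whatever the within-trial result. Within-trial results will be reported alongside, and uncertainty in the trial estimates and in the extrapolation will be propagated.*

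If the sponsor prefers to keep a condition, the minimum is to define it for outcomes and for costs, and to state what will be reported if it is not met, before any comparative data are seen. That is second best, because the horizon would still depend on the result.

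The cost is some health-economist time, and only where the model would otherwise have been skipped. Section 11.6.5 already sets out the model type, discount rate, use of parametric survival curves and reporting standard. Recruitment, data collection and the clinical analysis do not change.
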